### Ethics

The independent medical ethics committees of the participating hospitals have approved this FTMDT-trial protocol, with the approval number: 2010LSY No.6. All the procedures of this study are under the oversight of the Chinese Ministry of Health.

### Study outline

#### Interventions

##### Surgery

Much experience has been accumulated since the first laparoscopic colectomy in 2003 in Hangzhou center, as the number of all colorectal cancer surgery has been approximately up to 350 per year, including about 30% open surgery and 60% laparoscopic surgery. Shaoxing center has done approximately 400 laparoscopic colorectal surgeries since developed in 2004 and Wenzhou center approximately 300 since 2005.

In this study, open and laparoscopic surgery will be performed according to the principles of NCCN Clinical Practice Guidelines in Oncology ™ Colon Cancer V.2.2009 and there are 8 colorectal surgeon specialists, all of whom are Attending Surgeons ([name], [name], [name], [name], [name], [name], [name], [name]). The former five of them are for laparoscopy and they have performed laparoscopic operations in colorectal cancer with a minimum of 20 as suggested by the ASCRS [20,21].

##### Perioperative treatment

Patients in groups III and IV will receive conventional perioperative treatment, while patients in groups I and II will receive the fast track perioperative treatment, which will be provided by trained doctors and nurses separately.

The essence of the fast track perioperative treatment can be represented from 3 periods, 1. Preoperation, psychological optimism and information of the fast track treatment to patients, less time fasting, oral carbohydrate loaded liquids. 2. Intraoperation, combined anesthesia consisting of epidural and general anesthesia with the use of morphine minimized as far as possible, minimal use and early removal of nasogastric tube, drains and catheter, body warming as well as intravenous fluid warming. 3. Post operation: pain management without opioid, early feeding rehabilitation, restriction of intravenous fluid infusion, early ambulation.

The comparison of fast track and conventional perioperative operation treatments are summarized in Table 1.

**Table 1 T1:** Checklist of fast track and conventional perioperative operation treatments

Time	Fast track treatment	Conventional treatment
Preadmission	-Psychological optimism	-No psychological optimism

(After randomization)	-Pre-assessment for risk adjustment	-Pre-assessment for risk adjustment
	
	-Anesthesiologic information of combined anesthesia consisting of thoracic epidural and general anesthesia	-No Anesthesiologic information of general anesthesia
	
	-Information of the fast track treatment and the informed consent	-Information of the conventional treatment and the informed consent
	
	-Guided tour of fast track wards	-No tour
	
	-Operation schedule	-Operation schedule

Preoperation	-Bowel preparation: semiliquid diet 1 days before operation	-Bowel preparation: liquid diet 1-2 days before operation
	
	- Enemas:	-Enemas:
	
	Polyethylene Glycol-Electrolyte Powder ^® ^(Hengkang Zhengqing™, Jiangxi Hygecon Pharmacy CO., Ltd, Shangrao, CN) the afternoon before surgery,2 boxes mixing with 2,000 ml warm drinking water	Polyethylene Glycol-Electrolyte Powder ^® ^the afternoon before surgery, 2 boxes mixing with 2000 ml warm drinking water
	
	-Fasting: last meal 2 h before operation	-Fasting: last meal 10 h before operation
	
	-Complete Enteral Nutritional Emulsion Supportan (TPF-T) ^® ^(Supportan™, Sino-Swed Pharmaceutical CO. Ltd, Wuxi, CN) 600 ml or Fresubin Diabetes (TPF-D) ^® ^(Fresubin Diabetes™, Sino-Swed Pharmaceutical CO. Ltd, Wuxi, CN) 500 ml (especially for patients with diabetes mellitus) p.o. 8 h before operation	- No oral intake in the operation day
	
	- 10% Glucose 400 ml p.o. 2-3 h before operation	- No oral intake in the operation day
	
	- Nasogastric tube 0.5 h before operation for Gastrointestinal decompression	- Nasogastric tube 0.5 h before operation for Gastrointestinal decompression

Intraoperation		

-Anesthetic managemen	- Placement of epidural catheter (T6-L1), depending on the surgical resection); test-dose (3 ml of 2% lidocaine (Hefeng™, Harvest Pharmaceutical CO. Ltd, Shanghai, CN)) followed by continuous infusion (10 ml of 0.5% or 0.75% ropivacaine(Naropin™, APP Pharmaceuticals, LLC., Schaumburg, IL) according to the age and size of the patient before surgical incision	- No thoracic epidural anesthesia
	
	- Balanced Combination with general anesthesia: intravenous midazolam (Liyuexi™, Nhwa Pharmaceutical Co., Ltd., Xuzhou, CN) (0.1 mg/kg), target-controlled infusion (TCI) of propofol (Diprivan™, AstraZeneca Pharmaceutical Co., Ltd., Shanghai, CN) (4-8 μg/ml), sufentanil (Fukang™, Humanwell Pharmaceutical Co., Ltd., Yichang, CN) (0.5-1 µg/kg), rocuronium (Esmeron™, Organon Teknika B.V., Oss, NL) (0.6-0.9 mg/kg).	- Normal General anesthesia: intravenous midazolam (0.1 mg/kg), target-controlled infusion (TCI) of propofol (4-8 μg/ml), sufentanil 0.5-1 µg/kg, rocuronium (0.6-0.9 mg/kg).
	
	The patients were ventilated mechanically.	The patients were ventilated mechanically.
	
	Anesthesia was maintained propofol TCI (2-4 μg/ml), remifentanil (0.02-0.03 μg/kg/min) and intermittent boluses of rocuronium.	Anesthesia was maintained propofol TCI (2-4 μg/ml), remifentanil (Ruijie™, Humanwell Pharmaceutical Co., Ltd., Yichang, CN) (0.02-0.03 μg/kg/min) and intermittent boluses of rocuronium.
	
		As equally depth of anesthesia is also needed in conventional treatment group with no thoracic epidural anesthesia, more drug dosage of general anesthesia is used.
	
	- Morphia as little as possible	- No restriction of Morphia use
	
	- Monitoring: (Datex Ohmeda™ S/5 Anesthesia Monitor (Datex-Ohmeda Division, Instrumentarium Corp., Helsinki, Finland)) consists of electrocardiogram (ECG), heart rate (HR), respiratory rate, arterial pressure (BP), SpO2, end-tidal CO2 (etCO2), and bispectral index (BIS). - The target concentration of propofol:keep BIS between 40 and 60 to maintain adequate hypnosis. - Perioperative hypotension:systolic blood pressure (SBP) < 80 mmHg or a decrease of 30% baseline value and was treated with reduction of anesthetics, fluid supplement, and a bolus dose of ephedrine (Mahuangsu™, Northeast Pharmaceutical Co., Ltd., Shenyang, CN) (10 mg, IV). If SBP was above 160 mmHg or increase > 30%, an increase of propofol or remifentanil infusion was given to deepen anesthesia.	- Monitoring: the same as fast-track group

-Antibiotic prophylaxis	- Yes,	- Yes

-Surgical management	-Laparoscopic/open surgery as randomization	-Laparoscopic/open surgery as randomization

- Warming	- Yes, body warming by thickening quilt as well as intravenous fluid warming	- No body and intravenous fluid warming

- Drains	- Minimal use and early removal of abdominal drains	-Regularly use and removal of abdominal drains

- Fluid infusion	- Totally ≤ 1,500 ml during operation	- No restriction

Postoperation		

- Pain management	-Patient-controlled continuous epidural analgesia with a 5 ml/h continuous infusion of 0.15% ropivacaine and a bolus dose of 2.5 ml (locktime 15 min) until 48 h after operation, paracetamol (Tylenol™, Johnson & Johnson Pharmaceutical Co., Ltd., Shanghai, CN) p.o. when needed	-Patient-controlled intravenous analgesia with a 4 ug/h continuous infusion of sufentanil and a bolus dose of 1.5 μg (locktime 15 min)
		
		-Bucinperazine (QiangtongdingTM, Northeast Pharmaceutical Co., Ltd., Shenyang, CN) or Morphine (Mafei™, Northeast Pharmaceutical Co., Ltd., Shenyang, CN) intramuscular injection when patient-controlled intravenous analgesia isn't enough for pain control

- Diet	- Chewing gum 1 piece tid p.o.	-No chewing gum
	
	- At least 10% Glucose 200 ml p.o. within 24 h after operation	- Fasting until flatus
	
	-Liquid diet and Enteral Nutritional Emulsion Supportan 200 ml or Fresubin Diabetes 300 ml (especially for patients with diabetes mellitus) p.o. the next day of operation	- Liquid diet after flatus
	
	- Diet rehabilitation as early as possible (dose increase of Enteral Nutritional Emulsion or when needed)	- Normal diet after defecation

- Intravenous fluid infusion	- Stop intravenous high energy fluid infusion after dosage of Enteral Nutritional Emulsion Supportan ≥ 600 ml or Enteral Nutritional Emulsion Fresubin Diabetes ≥ 500 ml	- Intravenous high energy fluid infusion on daily basis and continuing until adequate oral intake
	
	- No intravenous High-energy Nutrient Fluid after 72 h post-surgery	
	
	- Restricting and avoiding excessive intravenous fluid infusion, keeping body weight as pre-surgery	

- Energy	- Keep the total energy intake (both diet and intravenous fluid infusion) 25-30 kcal/kg/day	- Keep the total energy intake (both diet and intravenous fluid infusion) 25-30 kcal/kg/day

- Nasogastric tube and urethral catheter	-Remove nasogastric tube as soon as the end of operation	- Remove nasogastric tube after 1st flatus postoperation

	- Remove urethral catheter within 24-48 h after operation	-Remove urethral catheter when 1st time meet: patient have the feeling of automatic micturition and ≧200 ml after valving-on urethral catheter

- Ambulation	- Forced ambulation within 24 h post-surgery, no time restriction	- No ambulation scheme
	
	- Ambulation time ≥ 1 h per day, and increasing day by day	
	
	- Patients walking to weight themselves every day	

Adjuvant		

chemotherapy	- Xelox	- mFolfox6
	
	- repeat every 3 weeks for 8 cycles	- repeat every 2 weeks for 12 cycles
	
	- Regimen	- Regimen
	
	Oxaliplatin 130 mg/m2 day 1, Capecitabine (Xeloda™) 850-1,000 mg/m2 twice daily for 14 days -	Oxaliplatin (Eloxatin^TM^) 85 mg/m2 IV over 2 hours, day .1 Leucovorin (Tongao™) 400 mg/m2 IV over 2 hours, day 1. 5-FU (Jinyao™) 400 mg/m2 IV bolus on day 1, then 1,200 mg/m2/day × 2 days (total 2,400 mg/m2 over 46-48 hours) continuous infusion
	
	- No peripherally inserted central catheter (PICC)	- Peripherally inserted central catheter and care of PICC in outpatient clinic every week
	
	- Hospitalization no more than 24 h each cycle	- Hospitalization for 3 days each cycle

##### Adjuvant chemotherapy

In this study, adjuvant chemotherapy for III stage or high-risk II stage pathologically established colorectal cancer includes Xelox and mFolfox6, both of regimens which in accordance with NCCN Clinical Practice Guidelines in Oncology ™ Colon Cancer V.2.2009.

(a) mFolfox6 (repeat every 2 weeks for 12 cycles)

Oxaliplatin (Eloxatin™, Sanofi-aventis, Hangzhou, CN) 85 mg/m^2 ^IV over 2 hours, day 1

Leucovorin (Tongao™, Hengrui medicine Co., Ltd, Lian Yuan-gang, CN) 400 mg/m^2 ^IV over 2 hours, day 1

5-FU (Jinyao™, Tianjin KingYork Amino Acid Co., Ltd. Tianjin, CN) 400 mg/m^2 ^IV bolus on day 1, then 1,200 mg/m^2^/day × 2 days (total 2,400 mg/m^2 ^over 46-48 hours) continuous infusion

(b) Xelox, also known as CapeOX (repeat every 3 weeks for 8 cycles)

Oxaliplatin 130 mg/m^2 ^day 1, Capecitabine (Xeloda™, Roche, Shanghai, CN)

850-1,000 mg/m^2 ^twice daily for 14 days

##### Patient pathway

All the patients in the FTMDT trial will go through as depicted in the flowchart (Figure 1)

**Figure 1 F1:**
[figure not shown]
**The FTMDT trial flowchart**.

### Statistical analysis

#### Sample size calculation

Hospital stay is the primary endpoint. From the evidence in the researches [13,14,22-26], we estimate the hospital stay of laparoscopic and open surgery with Fast-track perioperative treatment is 6 and 8 days. Xelox chemotherapy has at most 1 hospitalization day for each cycle followed by taking Capecitabine orally at home, for a total of 8 cycles. Therefore, we calculate the hospital stay for groups I and II at 14 and 16 days. According to our previous research [27], the hospital stay of laparoscopic and open surgery with conventional perioperative treatment is 12 and 14 days. mFolfox6 chemotherapy requires at least 3 hospitalization days for each cycle, totally 12 cycles. So, we calculate the hospital stay of III and IV group is 48 and 50 days.

With the standard deviation of 6 days of mean hospitalization days, a total sample size of 218 would have a power of > 0.85 to detect a minimum reduction of 2 days in hospital stay among the 4 groups, using a 5% significance level. The III stage or high-risk II stage account for 64% of the total colorectal cancer patients [28], and these patients need the adjuvant chemotherapy according to the NCCN Clinical Practice Guidelines in Oncology-Colon Cancer Guideline 2009 (Version 2.2009) [29]. For this trial we will enroll 340 patients and have 85 patients in each group.

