### Study design

This FTMDT-trial is an open randomized prospective and controlled study with 2 × 2 balanced factorial design. Patients eligible for the criteria will be randomized into four study groups (1:1:1:1) according to the randomized figures generated by the SPSS 16.0, after the patients signing the informed consents: (I) Laparoscopic surgery with fast track perioperative treatment and Xelox chemotherapy; (II) Open surgery with fast track perioperative treatment and Xelox chemotherapy; (III) Laparoscopic surgery with conventional perioperative treatment and mFolfox6 chemotherapy; (IV) Open surgery with conventional perioperative treatment and mFolfox6 chemotherapy.

Chinese medical insurance system ensures that, hospitalization is suitable for payment and also for patients' interest. All patients in this study will receive hospitalized chemotherapy in each cycle.

This trial has the independent "third-party" for developing the randomization.

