### Primary and secondary endpoint measures

The primary outcome measure of this FTMDT-trial is the hospital stays, which is the overall hospitalization stay during treatment including both the hospital stay for the surgery and adjuvant chemotherapy.

We define the postoperative discharge day for the patients in the trial when they meet all of the discharge criteria, 1. Good pain control: NSR (Numeric Rating Scale) ≤ 3. 2. Tolerance of solid food, no need of intravenous fluid infusion. 3. Independent activities of daily living (ADL) to preoperative care level at least [18,19].

Secondary outcome measures are as follows, 1. Quality of life according to EORTC (European Organization for Research and Treatment) QLQ-C30 and QLQ-CR38 questionnaires, with the checkpoint frame, preoperation, 1 week post operation, 3-months post surgery and 6-months post surgery. 2. Chemotherapy related adverse events according to NCI CTCAE (Common Terminology Criteria for Adverse Events) Version3.0. 3. Surgical complications mainly include injury of the ureters, intraoperative transfusion, infection of incision, anastomotic leakage and readmission. 4. Hospitalization costs are calculated from the first day in hospital to the last day that adjuvant chemotherapy is finished.

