The NO16968/XELOXA study discovered that the Xelox chemotherapy used as an adjuvant chemotherapy for colorectal cancer become possible now, as it has a manageable tolerability profile in adjuvant setting [17]. In each cycle of Xelox chemotherapy, there is only 1 day hospital stay for intravenous Oxaliplatin and the Capecitabine intake from 1st to14th day can be done in home. And in mFolfox6 chemotherapy, each cycle needs 3 days hospital stay in China. Consequently, it can be seen clearly that the superiority of Xelox for shorter hospital stay with the similar Overall Survival (OS) to mFolfox6.

On this consideration, before this trial, [name] has been conducting an open nonrandomized prospective study comparing laparoscopic surgery with Xelox chemotherapy and open surgery with mFolfox6 chemotherapy for resectable colorectal cancer, and the interim analysis has proved that the former provides faster postoperative recovery and potentially sustained better quality of life throughout treatment [32].

In the view of the separate superiority of the laparoscopy, Fast-track perioperative treatment and Xelox chemotherapy, and the possibility of the integration of these three essential treatments in colorectal cancer, the new notion "Fast Track Multi-Discipline Treatment" (FTMDT) for the integration of these three treatments is promoted in this FTMDT trial. And this FTMDT model is supposed to substantially reduce the length of hospital stays with equal safety and effectiveness, gain the better long-term recovery outcomes, and give patients a better quality of life.

The 2 × 2 balanced factorial design for this randomized prospective controlled FTMDT study tries to answer 2 corresponding questions. The I and II groups versus the III and IV groups is designed to answer the research question "Is Fast-track multidiscipline treatment model safe and effective, compared to conventional treatment?", while the I group versus II group aims to answer "Is laparoscopy an essential component of FTMDT-trial and how important role does it play?"

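### With 218 patients, power for the 2-day laparoscopic-open difference is about 0.41 (group I vs II) or 0.69 (main effect), not above 0.85

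*Protocol article*

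**What the plan says.** The primary endpoint (Primary and secondary endpoint measures) is "the overall hospitalization stay during treatment including both the hospital stay for the surgery and adjuvant chemotherapy". The Sample size calculation section builds up planned means of 14 and 16 days for groups I and II (laparoscopic and open surgery, fast track, Xelox) and 48 and 50 days for groups III and IV (laparoscopic and open surgery, conventional care, mFolfox6).

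The claim under review, made for an SD of 6 days and a 5% level, is that "a total sample size of 218 would have a power of > 0.85 to detect a minimum reduction of 2 days in hospital stay". The sentence applies this to the four groups collectively. It names no test, no sidedness and no pair of groups. The section then gives 64% as the share of patients needing chemotherapy and sets enrolment at 340, with 85 per group.

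The Discussion links comparisons to questions. Groups I and II together against III and IV address the treatment model as a whole, "while the I group versus II group aims to answer" whether laparoscopy is an essential part of it. Study objectives lists the role of laparoscopy as the second of the trial's two questions.

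**The concern.** Every input needed to check the power is printed, and the figure does not follow from them. A 2-day difference with an SD of 6 is one third of a standard deviation, which is too small for about 55 patients per group, or 109 per pooled arm, to detect with power above 0.85.

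The laparoscopy question is what suffers. The Discussion says that if laparoscopy proves not to be essential, its use within fast track could be reconsidered to save cost. A non-significant I versus II result could feed that decision. A reader who trusts the stated power would put the chance of missing a real 2-day benefit below 15%, when it is about 59% for I versus II.

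**Working it through.** **Inputs**
- Total 218, power above 0.85, difference 2 days, SD 6, level 5%: Sample size calculation. The SD is read as the between-patient SD. If it were the SD of a group mean, power would be far lower.
- Equal allocation: Study design. This gives 218/4 = 54.5 per group, or 109 per surgical approach when groups are pooled.
- Planned means 14, 16, 48, 50: Sample size calculation. Laparoscopic versus open is 16 − 14 = 2 and 50 − 48 = 2. The package contrast is (48 + 50)/2 − (14 + 16)/2 = 49 − 15 = 34.
- Sidedness is not stated. Two-sided is assumed and one-sided is also shown.

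**Where 218 comes from.** 0.64 × 340 = 217.6, so 218 matches the expected number receiving chemotherapy among 340 enrolled.

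**Attempt to reproduce the stated power.** For two groups of n, power ≈ Φ(δ / (σ√(2/n)) − z), with z = 1.960 two-sided or 1.645 one-sided.

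*Group I vs II, n = 54.5.* Standard error 6 × √(2/54.5) = 1.149, and 2/1.149 = 1.740.
- Two-sided: Φ(1.740 − 1.960) = Φ(−0.220) = 0.413 (noncentral t: 0.407).
- One-sided: Φ(0.095) = 0.538 (t: 0.534).

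*Laparoscopic vs open main effect, 109 vs 109.* Standard error 6 × √(2/109) = 0.813, and 2/0.813 = 2.461.
- Two-sided: Φ(0.501) = 0.692 (t: 0.688).
- One-sided: Φ(0.816) = 0.793 (t: 0.791).

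The main-effect figure needs adjustment for package, as in a two-way analysis. Without it, each surgical arm mixes patients whose planned stays differ by 34 days, and SD 6 does not apply.

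**Overall four-group F test, N = 218**, with noncentrality λ = 54.5 × Σ(mᵢ − m̄)²/36 on 3 and 214 degrees of freedom:

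| Pattern of means | Largest gap (days) | Σ(mᵢ − m̄)² | λ | Power |
|---|---|---|---|---|
| 0, 1, 1, 2 | 2 | 2 | 3.03 | 0.27 |
| 0, 0, 0, 2 | 2 | 3 | 4.54 | 0.40 |
| 0, 0, 2, 2 | 2 | 4 | 6.06 | 0.51 |
| 0, 2, 2, 4 | 4 | 8 | 12.1 | 0.84 |
| 0, 2, 4, 6 | 6 | 20 | 30.3 | 0.998 |
| 14, 16, 48, 50 (planned) | 36 | 1160 | 1756 | 1.00 |

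When no two groups differ by more than 2 days, the most favourable pattern (0, 0, 2, 2) gives 0.51.

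**What power 0.85 would need (two-sided)**
- Patients per compared arm: 2 × (1.960 + 1.036)² × 36/4 = 161.6, so 162. That is 324 for the main effect, or 4 × 162 = 648 over four equal groups for I vs II.
- Detectable difference with 218 patients: 2.996 × 1.149 = 3.44 days (I vs II) or 2.996 × 0.813 = 2.44 days (main effect).
- Largest SD compatible with the claim: 2/(2.996 × √(2/54.5)) = 3.5 or 2/(2.996 × √(2/109)) = 4.9 days.

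**If all 340 were analysed and SD 6 still held (two-sided):** 85 vs 85 gives 0.58, and 170 vs 170, package-adjusted, gives 0.87.

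**The case against.** The strongest defence is that the sentence names no test and speaks of a minimum difference among four groups. It can be read as an overall test in which 2 days is only the smallest step between groups. Means of 0, 2, 2, 4 then give 0.84, and 0, 2, 4, 6 give 0.998. This stands far enough to rule out saying that no reading whatever exceeds 0.85. It does not rescue the claim: these powers come from gaps of 4 to 6 days, neither pattern matches the planned means, and a significant overall test would not show a 2-day laparoscopic-open difference.

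A second objection is that I versus II is named only in the Discussion, and that a 2 × 2 factorial design makes the main effect an equally natural target. That is fair, and is why both figures are given. Neither reaches 0.85.

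A third is that 340 patients are enrolled and the main effect in all 340 has power 0.87. A reader might infer that the power was worked out for 340 and then attached to 218. The article does not say so. Nor can 0.87 be adopted as it stands. The primary endpoint is total stay, and about 36% of patients would have no chemotherapy stay, so mixing them in would probably raise the SD. Moving to surgical stay would change the endpoint, and the article gives no SD for it.

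**Conclusion.** The stated power is wrong for any direct laparoscopic-open comparison with 218 patients. It is about 0.41 for I versus II and about 0.69 for the package-adjusted main effect (two-sided), or about 0.53 and 0.79 one-sided. The corresponding two-sided risks of missing a true 2-day benefit are about 59% and 31%. These figures rest on a between-patient SD of 6, equal groups, and an analysis of 218 patients as the power sentence states.

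A reader might infer that the whole trial is underpowered. The article does not support that: I+II versus III+IV is planned at 34 days against an SD of 6 and has power of about 1. The defect is confined to the second study question.

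**What to change.** In the Sample size calculation section:
1. Name the comparison that carries the 2-day difference, the test and its sidedness. If it is the main effect, state that the analysis adjusts for treatment package.
2. Replace the power above 0.85 at 218 patients with about 0.41 (I vs II) or about 0.69 (package-adjusted main effect), or give the difference detectable at 0.85 power: about 3.4 or 2.4 days.
3. Say that the comparison of I+II with III+IV is amply powered, and that a null laparoscopy result would not be conclusive.
4. Quote 0.58 (85 vs 85) or 0.87 (170 vs 170) for all 340 patients only as conditional on an SD of 6 holding there, with the endpoint named.

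This costs a rewording and no extra patients. It leaves the laparoscopy comparison underpowered for 2 days but reports that openly. Reaching 0.85 would be a separate decision on sample size.

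### The four-group comparison used to size the primary endpoint matches neither contrast assigned to the two research questions, and the laparoscopy contrast (I vs II) has power of about 0.41, not > 0.85

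*Protocol article*

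**What the plan says.** The primary endpoint is total time in hospital: "The primary outcome measure of this FTMDT-trial is the hospital stays, which is the overall hospitalization stay during treatment", covering the surgical admission and the chemotherapy admissions (Primary and secondary endpoint measures).

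The Sample size calculation gives planned means of 14, 16, 48 and 50 days for groups I to IV and an SD of 6 days. It states that "a total sample size of 218 would have a power of > 0.85". The effect and the error level attached to that power are worded as follows: "to detect a minimum reduction of 2 days in hospital stay among the 4 groups, using a 5% significance level". It names no test and no contrast.

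The Discussion links each research question to a contrast. On the fast-track model: "The I and II groups versus the III and IV groups is designed to answer the research question" of whether it is safe and effective. On laparoscopy: "while the I group versus II group aims to answer" whether it is an essential component and how much it contributes.

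Study design describes the trial as an "open randomized prospective and controlled study with 2 × 2 balanced factorial design".

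**The concern.** The comparison that fixes the sample size should be the one that answers the question. Here the sizing sentence refers to all four groups at a single 5% level, while the Discussion uses one pooled two-group contrast and one contrast between two of the four groups.

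The mismatch matters because the two planned effects differ so much in size. The fast-track and Xelox groups are expected to differ from the conventional groups by 34 days. Laparoscopic and open surgery are expected to differ by 2 days. A test across all four groups is dominated by the 34 days. The 2 days in the sizing sentence equals the planned laparoscopy difference (14 vs 16, 48 vs 50), so a reader will take the stated power to cover the laparoscopy question. If it does not, a non-significant I vs II result could be read as evidence that laparoscopy is dispensable when the trial had little chance of detecting the planned effect. A significant four-group result could equally be reported as success on the primary endpoint while saying nothing about laparoscopy.

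**Working it through.** **Inputs (Sample size calculation and Study design).** Means 14, 16, 48, 50; SD σ = 6, taken as the between-patient SD within a group; allocation 1:1:1:1; 218 analysed, so 218/4 = 54.5 per group and 109 per pooled pair. The 5% level is given without sidedness; two-sided is assumed, with one-sided values alongside.

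**1. Can the stated power (> 0.85 for 2 days at 218) be reproduced?**

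Two-group power (normal approximation) = Φ(δ/SE − 1.96), with SE = σ√(2/n).

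- 109 vs 109, δ = 2: SE = 6 × √(2/109) = 0.813; 2/0.813 = 2.461; Φ(0.501) = **0.69** (one-sided 0.79).
- One group vs one group, 54.5 each, δ = 2: SE = 6 × √(2/54.5) = 1.149; 2/1.149 = 1.740; Φ(−0.220) = **0.41** (one-sided 0.54).
- Four-group ANOVA with a largest difference of 2 days: noncentrality λ = n Σ(μᵢ − μ̄)²/σ². For means 0, 1, 1, 2, λ = 54.5 × 2/36 = 3.03 and power is 0.27. For 0, 0, 2, 2, λ = 54.5 × 4/36 = 6.06 and power is 0.51.

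No comparison with a 2-day difference reaches 0.85. The figure is exceeded only where the spread is larger: 0.998 for means rising in 2-day steps (0, 2, 4, 6), and about 1.00 for the planned means.

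**2. What does a four-group test on the planned means respond to?**

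- Planned means: the overall mean is 32 and the deviations are −18, −16, 16, 18. The sum of squares is 324 + 256 + 256 + 324 = 1160, so λ = 54.5 × 1160/36 = 1756.
- Laparoscopy effect removed, 34-day difference kept (15, 15, 49, 49): the sum of squares is 4 × 17² = 1156, so λ = 54.5 × 1156/36 = 1750.

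Removing the laparoscopy effect lowers λ by 4/1160, about 0.3%. Power is about 1.00 in both cases. The test would be significant almost surely whether or not laparoscopy shortens the stay.

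**3. The two Discussion contrasts at 218 analysed.**

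- I and II vs III and IV: planned difference (48 + 50)/2 − (14 + 16)/2 = 49 − 15 = 34 days; SE = 0.813; 34/0.813 ≈ 42. Power is about **1.00**.
- I vs II: planned difference 2 days; power **0.41**, as in step 1.

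For scale, 85% two-sided power for 2 days with SD 6 needs 2 × (1.960 + 1.036)² × 6²/2² = 161.6, so 162 per compared group, against 54.5 planned.

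**4. Side note on type I error.** The two contrasts are orthogonal. If neither null were false and either result alone could be claimed as success, the family-wise error would be 1 − 0.95² = 0.0975.

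**The case against.** The article does state its contrasts: the objectives pose two questions and the Discussion gives one comparison to each. On this view the sizing sentence is only loosely worded. It does not say that a four-group test decides the trial, and testing order and sharing of alpha may sit in a full protocol or analysis plan that is not shown. All of this stands, so the absence of a testing order is not part of the point. But the sizing sentence is current text that attaches a specific power to a specific difference, and that power is not true of the contrast the Discussion assigns to the laparoscopy question. An unseen plan could choose among the comparisons without making the published figure correct.

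The sentence might instead mean that 2 days is the smallest gap among the planned means, so that power refers to a four-group test on 14, 16, 48 and 50. Power is then indeed above 0.85, but it comes from the 34-day difference and gives no assurance about the 2 days.

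A reader might go further and infer an inflated family-wise error. The documents do not support that as the finding. No section says that either contrast alone makes the trial a success; they answer separate questions, and testing each at 5% is defensible. No section plans all six pairwise comparisons, or III vs IV, and the pooled I and III vs II and IV contrast is only suggested by the factorial label. The null for the first question is also nearly unattainable among chemotherapy recipients, because Table 1 sets at most 24 hours for each of 8 cycles against 3 days for each of 12.

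A reader might also credit I vs II with all 340 enrolled patients. The SD of 6 cannot simply be carried over: the article puts only 64% in need of chemotherapy, so 36% would have no chemotherapy stay and total stay would vary more within each group. The 218 matches the chemotherapy patients (340 × 0.64 = 217.6).

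**Conclusion.** The point holds as a mismatch between the sizing comparison and the contrasts that answer the questions. A four-group test is significant with probability about 1.00 on the planned difference between treatment models, whatever laparoscopy does, so it cannot answer the second question. The contrast assigned to that question, I vs II, has two-sided power of about 0.41 at 218 analysed against the stated > 0.85. A 109 vs 109 comparison of 2 days has 0.69. One-sided testing (0.54 and 0.79) does not close the gap. The first question is not at risk: its contrast has power of about 1.00.

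These figures rest on the article's own means and SD, equal groups, the 218 as the analysed number and a normal approximation. Type I error is a side note only: about 0.10, and only if either contrast alone could be claimed as success under a global null, which no section says and which Table 1 makes unrealistic.

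**What to change.** In the Sample size calculation, replace the four-group wording with the two Discussion contrasts on hospital stay: I and II vs III and IV first, then I vs II, each at two-sided 5%. State the power of each at the planned 218: about 1.00 and about 0.41. Add that a four-group test and any other comparison are supportive and cannot by themselves establish the laparoscopy claim.

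This takes two or three sentences and needs no extra patients or data. Putting the first contrast ahead costs the second essentially no power. There are two downsides: the stated power for the laparoscopy question becomes much less favourable, and a significant result in another comparison can no longer be claimed as confirmatory. Restating the power does not raise it. Keeping 0.85 for I vs II under the same assumptions would need 162 per group, or 4 × 162 = 648 analysed with equal allocation.
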